### Treatment details

#### Localization, simulation and immobilization

All patients will be immobilized in a comfortable and appropriate position to irradiate the metastatic lesion (s). Support and/or immobilization devices can be used to increase patient comfort or to ensure set-up reproducibility. The planning CT scan should be acquired with the patient in the same position and using the same immobilization/support device (s) as for treatment. Planning CT scan (without intravenous contrast for bone metastases but with intravenous contrast for lymph node metastases, unless contraindicated) will be done at < 3 mm intervals encompassing the region of interest with sufficient margin for treatment planning, a typical scan length should extend at least 10 cm superior and inferior beyond the treatment field borders.

#### Target contouring

The Gross Tumour Volume (GTV) will consist of the metastatic lesion (s) as visualized on CT. All available diagnostic imaging (PET-CT, MRI) is used in order to delineate the target structures as accurate as possible. No Clinical Target Volume (CTV) will be delineated. The Planning Target Volume (PTV) will be created by using a 3-dimensional margin on the GTV to allow for daily set-up variance and organ motion. Margins depend on the site irradiated with 3 mm margins for bony lesions and 5 mm for lymph nodes.

#### Organs at risk

Organs at risk (OAR) are contoured as visualized on the planning CT. The OAR depend on the localization of the metastases and should at least include all OAR (lying within the scanned range on the planning CT scan) for which dose constraints are described in the report of the AAPM task group 101 [12]. A Planning Organ at Risk Volume (PRV) expansion will be added to the OAR for setup uncertainty or organ motion. For mediastinum, liver, heart and kidney a PRV margin of 5 mm should be used. All dose constraints apply to this PRV. It is strongly recommended that dose constraints be not exceeded. If a dose constraint cannot be achieved due to overlap of the target with an OAR, the target coverage can be compromised in order to meet the constraint.

#### Treatment planning & prescription

SABR (static or rotational) treatment planning will be dependent the localization of the metastasis. Prescribing, recording and reporting of the doses will be consistent with the recommendations in Report 91 of the International Commission on Radiation Units and Measurements (ICRU) [13]. Treatment will be prescribed to the periphery of the target, i.e. 80% of the dose should cover 90% of the PTV. A dose inhomogeneity in the PTV overlapping with a PRV is allowed but 90% of the GTV should receive the prescribed dose. Maximum PTV dose up to 160% is allowed but all dose > 105% should lay within the PTV. Dose fall-off outside the PTV extending into normal tissue structures must be rapid in all directions and one should target a dose fall-off of 50% off the prescribed dose within 3 cm outside the PTV. The OAR dose constraints will be in accordance with the recommendations from the report of the AAPM task group 101 [12].

#### Delivery and verification

Treatment will be delivered with 6–10 MV photons of a linear accelerator using cone-beam CT set-up and on-line correction of patient’s position. No other radiotherapy than photon therapy is permitted. The same position and immobilization/support device (s) as used in the planning CT scan should be utilized.

#### Interruptions

Treatment interruptions will usually not be necessary and should be kept to a minimum. Rarely, (unexpected) toxicities or non-treatment-related events may require interruption of treatment at the discretion of the investigator. Every effort should be made to limit treatment interruptions to a maximum of 5 days (including weekends and national holidays). In case of treatment interruption, Treatment should be completed to the prescribed doses. The total number of fractions and the overall treatment time should be reported.

### Translational research

#### Required samples

From the second dose level on (3x10Gy), liquid biopsies will be collected throughout the course of this study for biobanking. The liquid biopsy in this study encompasses pheripheral blood samples (1 × 9 mL ethylenediaminetetraacetic acid (EDTA) tube and 1 × 9 mL cellular preparation tube (CPT)), to be taken at simulation, immediately after each fraction, approximately 2 weeks after the last fraction, and at 3 and 6 months follow-up.

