**Methods:**

The DESTROY-trial is a non-randomized prospective phase I trial determining a regimen of choice for patients with non-spine bone and lymph node metastases. A total of 90 patients will be included in three different treatment regimens. They will be offered stereotactic ablative radiotherapy in 5, 3 or 1 fractions. Dose-limiting toxicity will be recorded as primary endpoint. Acute and late toxicity, local response and local recurrence, and progression-free survival are secondary endpoints. Liquid biopsies will be collected throughout the course of this study from the second fractionation schedule on.

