**Discussion:**

Despite its almost universal use in (oligo-)metastatic patients, the level of evidence supporting radical local treatment in general, and stereotactic radiotherapy in particular, is low. This prospective phase I trial will evaluate different SABR regimens for metastases and the differences in immune-stimulatory effects.

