### Interventions

A minimum of thirty patients will be included for each dose level. The different treatment regimens and their biological effective doses (BED_10Gy_) and equivalent dose in 2 Gy per fraction (EQD_2Gy_) are presented in Table 2. Calculations for BED_10Gy_ and EQD_2Gy_ are made using an alpha/beta ratio of 10 and 2, respectively. An interval of at least 24 weeks from the first patient treatment to the next patient treatment at each dose level will be respected. In the meantime, more patients will be included in the previous dose level, in an effort to establish the secondary endpoints. In case 1 to 5 patients present with DLT at 6 months after SABR, 30 additional patients will be included at the same dose level.

**Table 2 Tab2:** Fractionation schedules

Level	Fractions	Interval	Dose/fraction	Total	BED_10Gy_	EQD_2Gy_
1	5	48 h	7	35	59.5	78.75
2	3	48 h	10	30	60.0	90
3	1	NA	20	20	60.0	110

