### Statistical analysis

#### Sample size

For each dose level, a minimum of 30 patients will be included. The maximal tolerated dose will be defined as the dose level below which at least 10 patients present with a DLT at 6 months after SABR.

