SABR is also often used for treating metastases from radioresistant tumors like renal cell carcinoma or malignant melanoma. Radioresistance may be overcome with dose escalation, particularly by increasing the dose per fraction [9]. A systematic review of Kothari ea. evaluating the use of SABR found excellent LC rates and low rates of toxicity for intracranial and extracranial metastatic renal cell carcinoma [26]. They reported a weighted one-year LC rate of 86% and grade 3–4 toxicities ranging from 0 to 4%. In the setting of oligometastasized malignant melanoma, there is less clinical data available. Nevertheless, a prospective study showed high rates of complete response and durable metastasis control with SABR for extracranial metastases of malignant melanoma, including bone and lymph node metastases [27]. Both for malignant melanoma and for renal cell carcinoma, LC rates achieved are comparable to those obtained with SABR for other histologies, suggesting a dominant mechanism of in vivo tumor ablation that overrides intrinsic differences in cellular radiosensitivity between histologic subtypes [28].

The concept of a risk-adapted approach for SABR fractionation regimens, using smaller fraction sizes for tumor locations that overlap with organs at risk for toxicity, has gained widespread acceptance. This concept is based on the assumption that fractionation relatively decreases the EQD2 for normal tissues. The results of this dose escalation trial, with increasing dose per fraction, can help to improve the risk-adapted approach for non-spine bone and lymph node metastases. Also important in this regard is the alpha/beta ratio of 10 used in the BED calculations, which is an estimate of the general alpha/beta ratio of tumor metastases. However, the available clinical data support the use of a lower alpha/beta for renal cell carcinoma, breast or prostate cancer, which would lead to a higher BED.

To keep the study protocol accessible to most metastasized patients, there is no limitation on the use of concurrent systemic treatment, but this gives a possible increase in acute or late toxicity.

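### The only pre-treatment blood sample is drawn at simulation, so at both sampled dose levels the first-fraction biomarker change also contains the planning interval

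*Protocol article*

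**What the plan says.** All references are to the protocol article.

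- **Required samples** limits blood collection to levels 2 and 3: "From the second dose level on (3x10Gy), liquid biopsies will be collected throughout the course of this study for biobanking". The draw times are "to be taken at simulation, immediately after each fraction, approximately 2 weeks after the last fraction, and at 3 and 6 months follow-up".
- **Table 3** agrees on the baseline. As far as the extracted table can be read, its one pre-treatment blood cross is under the pre-study column, and none is marked as taken before irradiation on the first treatment day. The table has no column for the 2-week draw that the text names.
- **Table 2** gives level 2 as three fractions of 10 Gy at 48 h intervals and level 3 as one fraction of 20 Gy.
- **Discussion** says of other therapy that "there is no limitation on the use of concurrent systemic treatment".
- **Abstract, Discussion** states what the samples are meant to inform: "This prospective phase I trial will evaluate different SABR regimens for metastases and the differences in immune-stimulatory effects".
- **Sample size**: "For each dose level, a minimum of 30 patients will be included".

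**The concern.** A before-and-after biomarker contrast is attributable to a fraction only if little else can happen between the two samples. Here the earlier sample is taken on the planning day and the later one after irradiation. Any shift in cytokines, cfDNA or immune cells over the planning interval is part of the measured change, and a systemic-therapy dose given in that interval could cause such a shift.

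The immediate response matters for the trial's own rationale. The Background reports that Trex1, which dampens immunogenicity, is induced by doses above 12–18 Gy. The fraction size at level 2 (10 Gy) lies below that range and at level 3 (20 Gy) above it. The response to the first fraction is thus a natural contrast between the two sampled levels.

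Within-patient change is also the sensible measure. The cfDNA section gives concentrations from 0.2 to 62.8 ng/μL, a 62.8/0.2 = 314-fold range that depends on tumour burden, so comparing post-treatment values alone would be weak. A baseline not drawn before irradiation cannot be obtained afterwards.

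**Working it through.** The plan states no figure for this component, so there is none to reproduce. The check lists the scheduled samples and the contrasts they allow.

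**1. Samples per patient**

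- Level 2: simulation; after fractions 1, 2 and 3; about 2 weeks; 3 months; 6 months. 1 + 3 + 3 = 7.
- Level 3: simulation; after the single fraction; about 2 weeks; 3 months; 6 months. 1 + 1 + 3 = 5.

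**2. Early contrasts available**

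| Contrast | Level 2 | Level 3 |
|---|---|---|
| Immediately before to immediately after fraction 1 | 0 | 0 |
| Between on-treatment draws, without the simulation sample | 3 | 0 |
| As above, also allowing the 2-week draw | 6 | 1 |

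The three on-treatment contrasts at level 2 are fraction 1 to 2, 1 to 3 and 2 to 3. All start after the first 10 Gy. The single contrast at level 3 runs from after the fraction to about 2 weeks, so it too starts after irradiation. None of them shows the effect of the first fraction.

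**3. What the drift does.** Let D be the mean change over the planning interval and E the effect of fraction 1. The change from simulation to after fraction 1 estimates D + E within each level. The difference between levels estimates (E3 − E2) + (D3 − D2). If D is the same at both levels it cancels; otherwise D3 − D2 remains as bias.

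**4. Illustration.** The drift sizes are assumed; n = 30 per level is the stated minimum, with every patient assumed sampled. Take E = 0, a two-sided 5% test, a normal approximation, and drift d in SDs of the paired change. With z = 1.96, the probability of a false finding is Φ(k − z) + Φ(−k − z), where

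- within a level, k = d√30;
- between levels, k = d/√(2/30), with d now the difference in drift.

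| d | Within a level | Between levels |
|---|---|---|
| 0 | 0.05 | 0.05 |
| 0.1 | 0.085 | 0.067 |
| 0.2 | 0.195 | 0.121 |
| 0.3 | 0.376 | 0.213 |
| 0.5 | 0.782 | 0.491 |

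For example, at d = 0.3 within a level, k = 0.3 × 5.477 = 1.643, and Φ(−0.317) + Φ(−3.603) = 0.376.

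**5. Precision, also on assumed values.** The variance of a change is 2·SD²·(1 − r), with r the within-patient correlation. If r is 0.9 for samples about an hour apart and 0.6 to 0.8 for samples 1 to 2 weeks apart, the variance is 0.2 SD² against 0.4 to 0.8 SD², or 2 to 4 times as large. This applies only to the immediate contrast. For the draws at 2 weeks, 3 and 6 months, either baseline is weeks or months from the later sample.

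**The case against.** The strongest case on the other side has four parts.

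- **The samples are for biobanking, and the article writes no change-from-baseline analysis.** This stands. Biomarkers are neither a primary nor a secondary endpoint. But the abstract promises an evaluation of differences in immune stimulation, and the draw times limit any analysis of the bank.
- **The time from simulation to fraction 1, and the recording of systemic-therapy dates, may be in the full protocol.** This also stands, and their absence here is no fault. A short fixed interval would shrink the drift. The point rests on the stated draw times, not on this silence.
- **Common drift cancels between levels.** Correct, as step 3 shows. Nothing in the article shows that planning intervals or systemic therapy differ between the levels. Because the levels are non-randomized and opened in sequence, it cannot be ruled out either.
- **Changing the baseline midway could create the bias it is meant to remove.** If level 2 patients keep a simulation baseline and level 3 patients get a same-day one, drift that would have cancelled becomes a difference between levels. This is right and shapes the fix.

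A reader might also infer that the gap is special to level 3, or that level 3 has no other early contrast. The schedule does not support either reading. Level 2 equally lacks a clean first-fraction contrast, and level 3 does have the contrast from after the fraction to about 2 weeks. Nor would a new baseline remove calendar-time changes in systemic practice, which confound the sequential levels wherever the baseline sits.

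**Conclusion.** The concern holds as a low-priority design weakness at both sampled levels. The change from the only pre-treatment sample to the first post-fraction sample cannot separate the fraction-1 effect from the planning interval. Level 3 additionally has no on-treatment contrast independent of simulation.

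Within-level effects are exposed to any drift; the comparison of level 2 with level 3 is exposed only to drift that differs between them. The actual size cannot be computed, because the article gives neither the interval nor any marker variability, and it may be small. The probabilities and variance ratios above show sensitivity to assumed inputs and are not estimates for this trial. The maximum tolerated dose, toxicity, local response and failure, and progression-free survival are unaffected.

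**What to change.** 1. At both sampled levels, take the baseline blood sample on the first treatment day, immediately before fraction 1.
2. If level 2 sampling has already begun, keep the simulation draw at both levels and add the pre-fraction-1 draw. Level 3 can then be compared with all level 2 patients on the simulation baseline, and with later level 2 patients on the same-day baseline. Flag which patients have which samples.
3. Compare the levels at the times both share: before fraction 1, after fraction 1, about 2 weeks after the last fraction, 3 months and 6 months. Report the level 2 draws after fractions 2 and 3 descriptively.
4. Record the date of the last systemic-therapy dose with each draw, if the full protocol does not already do so.
5. Reconcile Table 3 with the text on the 2-week draw, since it supplies level 3's only early contrast that does not use simulation.

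**Cost.** Moving the draw keeps the totals at 7 and 5 samples per patient, on a visit the patient already attends, with two draws on one day. Keeping the simulation sample as well adds one draw, giving 8 at level 2 and 6 at level 3.

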#### Assessment of circulating cytokines

One EDTA blood tube generally yields 4 mL of plasma, which can be split in half for circulating free deoxyribonucleic acid (cfDNA) analysis (vide infra) and for the measurement of protein concentrations of circulating cytokines. This latter can be done using Luminex assays, and requires and input volume of 100 μL per assay, allowing 20 cytokines to be profiled using 2 mL of plasma. The plasma must be kept at − 80 °C. Under these conditions, most cytokines are stable for up to 2 years under the premises that freeze-thaw cycles are avoided [11].

#### cfDNA for shallow whole genome sequencing

For cfDNA low-pass whole genome sequencing, cfDNA first needs to be extracted from plasma samples with a typical starting volume of 1 mL. The cfDNA concentrations from 1 mL of plasma, in a final elution volume of 50 μL, are highly variable and depend on tumour burden (range 0.2 ng/μL to 62.8 ng/μL). Hence the calculated cfDNA yield from 1 mL of plasma ranges from 10 ng to 3140 ng. For low-pass whole genome sequencing using the Thru-PLEX™ DNA-seq Library Kit, 2 ng of cfDNA is required, suggesting that 1 mL of plasma should be sufficient in most cases. To avoid patient drop-out due to insufficient starting material, biobanking 2 mL of plasma aliquoted in units of 400 μL at -80oC is advisable. [12].

#### Flow cytometry analysis of immune cells

Peripheral blood mononuclear cells (PBMC) can be isolated from heparinized venous blood by centrifugation on a Ficoll-Hypaque gradient within 4 h of venepuncture. The PBMCs can cryopreserved in liquid nitrogen in heat-inactivated foetal bovine serum (FBS) supplemented with 10% dimethyl sulphoxide (DMSO) until analysis. Upon analysis, cells are thawed by submersion at 37° for 1–2 min and resuspended in a medium containing Iscove’s Modified Dulbecco’s Medium supplemented with 20% FBS and 1% glutamine [13].

### Statistical analysis

#### Sample size

For each dose level, a minimum of 30 patients will be included. The maximal tolerated dose will be defined as the dose level below which at least 10 patients present with a DLT at 6 months after SABR.

#### Data analysis

All data will be prospectively collected. Electronic case report forms will be used; database will be excel-based and Access-based. Statistics will be carried out using the latest version of SPSS. The primary endpoint MTD will be evaluated at 6 months after the end of SABR. The incidence of acute and late toxicity will be recorded. Chi-square test will be used to find out the significance of results. Disease free survival will be calculated using Kaplan Meier actuarial analysis. Survival times are defined from the date of start of the treatment until an event or last follow up.

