### Time schedule and follow-up

The aim is to recruit the necessary number of patients within a timeframe of 48 months. Follow-up of these patients will be life-long in order to correctly estimate the secondary endpoints (Table 3). Patients are seen centrally by the clinical research physician at 3 and 6 months after SABR. At 6 months, repeated imaging is performed in the study to assess local control. All imaging is considered standard and should minimally include a CT of the irradiated lesion (s) but might also include MRI and/or PET-CT (with whatever relevant tracer) if standard for that malignancy. Reports on acute toxicity will be expected within 2 months after closure of the trial.

**Table 3 Tab3:** Time schedule

	TRIAL PERIOD						FOLLOW-UP		
	Screening visit	Pre-study	During study				Year 1	Year 2	Year 3 till ∞
			Every SABR fraction	Last day of SABR	3 months after SABR	6 months after SABR	Every 3 months	Every 6 months	yearly
Informed consent	x								
Clinical examination	x			x	x	x	x	x	x
Registration of toxicity		x		x	x	x	x	x	x
Registration of QoL		x		x	x	x	x	x	x
Blood sample		x	x	x	x	x			
Imaging						x			

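### The planned chi-square test of late-toxicity incidence fixes no common time point, so across sequentially filled levels it mixes regimen with length of follow-up

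*Protocol article*

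**What the plan says.** The Data analysis section states the method for toxicity: "The incidence of acute and late toxicity will be recorded. Chi-square test will be used to find out the significance of results". The time-to-event method is given to another outcome: "Disease free survival will be calculated using Kaplan Meier actuarial analysis". No time point, cut-off date or allowance for death is attached to the toxicity comparison.

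The design around it is as follows.

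- The abstract's Methods describe a "non-randomized prospective phase I trial" and the total: "A total of 90 patients will be included in three different treatment regimens".
- Interventions: "A minimum of thirty patients will be included for each dose level". Levels open in sequence with a 24-week interval, and accrual continues at the previous level meanwhile. If 1 to 5 patients have a dose-limiting toxicity (DLT), "30 additional patients will be included at the same dose level".
- Time schedule and follow-up plans recruitment over 48 months and adds: "Follow-up of these patients will be life-long in order to correctly estimate the secondary endpoints". Every patient is seen at 3 and 6 months.
- Objectives gives DLT a window of 24 weeks after SABR, the same for every patient.
- The Discussion cites a review of renal cell carcinoma metastases with grade 3–4 "toxicities ranging from 0 to 4" percent. It also cites bone series with no late toxicity of grade 3 or more.

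**The concern.** Late toxicity accrues with time. When levels are filled in sequence and nobody's follow-up is capped, patients at level 1 have been watched longest and patients at level 3 shortest on any single analysis date. A test on the proportion with an event takes no account of time at risk or of death before an event could occur. Two regimens with identical late toxicity can then look different, and a regimen with more late toxicity can look no worse if it was enrolled last.

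The direction matters. Table 2 gives level 3 the highest EQD2 (110, against 78.75 and 90), and the Discussion describes an escalation in dose per fraction. The distortion lowers the apparent late toxicity of the level where an excess would matter most. Comparing the regimens on acute and late toxicity is the article's declared aim.

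**Working it through.** **The plan's own figure.** 3 levels × 30 = 90, which agrees with the abstract. No alpha, power or effect size is stated, so 30 per level cannot be derived further.

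**Gap in follow-up between levels 1 and 3 (assumed accrual).**

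- Equal thirds of 48 months: mean entry at months 8, 24 and 40, so the gap is 40 − 8 = 32 months.
- The 24-week interval, read as spacing between levels, is about 5.5 months. Fastest filling gives mean entries at about 2.8, 8.3 and 13.8 months, a gap of about 11 months.
- Using all 48 months with two levels at 5.5 months leaves 37 months for the third. If that is level 1, mean entries are 18.5 and 45.2, a gap of about 27 months. If it is level 2, they are 2.8 and 45.2, a gap of about 42 months.

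**Expected crude incidence when all levels have the same hazard.** Let h be the late-toxicity hazard and d the death rate, both per year, and k = h + d. With entry uniform over a block and potential follow-up running from a to b years:

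incidence = (h/k) × [1 − (e^(−ka) − e^(−kb)) / (k(b − a))]

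Assumed: h = 0.05, d = 0, 16-month blocks, cut-off at month 54. Potential follow-up is 38–54, 22–38 and 6–22 months.

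- Level 1: 1 − (0.8536 − 0.7985)/0.0667 = 17.4%
- Level 2: 11.7%
- Level 3: 1 − (0.9753 − 0.9124)/0.0667 = 5.6%

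With d = 0.25 per year (median survival ln 2/0.25 = 2.8 years) they are 11.4%, 8.7% and 4.8%.

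**Rejection by the nominal 5% three-level Pearson test**, 30 per level, equal hazards, by enumerating every possible table:

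| Hazard per year | Block (months) | Cut-off (month) | No deaths | Deaths 0.25 per year |
|---|---|---|---|---|
| 10% | 16 | 54 | 40% | 17% |
| 5% | 16 | 54 | 20% | 8.7% |
| 5% | 16 | 72 | 15% | 5.9% |
| 5% | 16 | 108 | 10% | 4.9% |
| 2% | 16 | 54 | 8.1% | 5.1% |
| 1% | 16 | 54 | 4.5% | 2.2% |
| 5% | 5.5 | 54 | 5.9% | 4.4% |

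Low rejection has two different causes here. At month 108 with deaths the bias itself has faded: at 5% per year the level 1 to level 3 incidence ratio is 15.3/13.6 = 1.1. At 1% per year and month 54 the ratio is still 3.8/1.2, about 3.2 (no deaths), and the test is quiet only because events are few.

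**Masking.** Keep the month-54 schedule without deaths, but set level 3's hazard at 10% per year against 5% elsewhere. Crude incidence becomes 17.4%, 11.7% and 11.0%: the level with twice the hazard shows the lowest figure. At a fixed 12 months the expected values are 1 − e^(−0.05) = 4.9% at levels 1 and 2 and 1 − e^(−0.10) = 9.5% at level 3, in the right order.

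**Sparse severe events (minor).** At the cited 0–4%, expected events are 30 × 0 to 0.04 = 0 to 1.2 per level (0 to 2.4 with 60). For events of 0, 0 and 3 in 30 each, chi-square = 6/1 + 6/29 = 6.21 on 2 df, p = 0.045; the conditional exact p is 3 × C(30,3)/C(90,3) = 0.104. Over all possible tables, however, the true size of the three-level test is 2.0% at a 2% rate and 3.6% at a 4% rate, both below 5%.

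**The case against.** The strongest reply is that the sentence does not say the incidence is counted at an arbitrary cut-off. Late time points, grade thresholds and contrasts are details that a condensed article leaves to the full protocol or analysis plan. A chi-square test at a common landmark would remove the difference in potential follow-up. This has force, and it is why the point is put as a comparison that needs a time point, not as a proven error in results. But the article does state a method for late toxicity, keeps the time-to-event method for disease-free survival, and ties the secondary endpoints to life-long follow-up. As written, nothing holds the comparison to equal follow-up.

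Second, the inflation needs a hazard of about 5% per year or more, which no document supports for severe events; the cited bone series had no late grade 3 or higher toxicity. That stands for grade 3–4 events. Late toxicity is to be graded by CTCAE with no lower limit, so more frequent lower-grade events may be tested, and for those the higher hazards are possible.

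Third, preferring a conditional exact test on sparse tables is largely a matter of taste. For 4 against 0 events in 30 each, chi-square gives p = 0.038, Fisher 0.112, and the unconditional Barnard test 0.046. That stands: most of the gap is the conservatism of the conditional test.

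Fourth, the maximum tolerated dose rests on a count of DLTs and not on a chi-square test. That also stands; the primary endpoint is untouched.

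**Conclusion.** The point holds for late toxicity. The stated analysis lets dose level and length of follow-up be confounded, and the bias runs toward making the last-enrolled level look better. Under equal 16-month blocks, a month-54 cut-off and a common 5% per year hazard, false rejection is about 20% without deaths and 9% with deaths at 0.25 per year. It is near or below 5% at 1% per year, and with a month-108 cut-off plus deaths; at 2% per year it is 8% without deaths and 5% with them. Accrual pattern, hazard, death rate and cut-off are all assumptions.

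A reader might infer more, and the documents do not support it:

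- That level 1 is followed 32 months longer. That figure assumes equal thirds of a planned 48 months; about 11 to 42 months is plausible.
- That level 1 must look worse by design. This depends on a fairly early common cut-off and similar hazards.
- That all the toxicity testing is invalid. Acute toxicity and DLT have a fixed 24-week window with visits at 3 and 6 months for everyone, so unequal follow-up does not reach them.
- That few events inflate the error rate. Sparseness alone keeps the chi-square test below its nominal 5%.

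This should be corrected, but it does not threaten the primary endpoint.

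**What to change.** In Data analysis, replace the chi-square sentence for late toxicity. Report, per level, the cumulative incidence from start of SABR with death as a competing event, with confidence intervals, at the same fixed times for all levels (for example 12 and 24 months). Start of treatment is already the time origin that section uses for survival times. Tie the data cut-off to the chosen times: on the 16-month-block schedule, level 3 has at most 54 − 32 = 22 months of follow-up at month 54, so a 24-month estimate needs a later cut. Label all between-level comparisons descriptive, because allocation is sequential and not randomised.

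As a minor addition, give exact confidence intervals for acute grade 3–4 toxicity and DLT at each level. With 0 events in 30, the upper 95% limit is 1 − 0.025^(1/30) = 11.6%, which keeps a clean level from being read as proof of no risk.

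The cost is a change of wording and a few lines of analysis code. The trial gives up a single p-value on total late toxicity. Sample size, schedule and clinical conduct do not change.
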